#### SAME Study Cocreators

Table 1 shows an overall presentation of participants in the SAME study. We aim to achieve equally powered partnerships between participants and researchers, shifting participants and researchers into the role of cocreators [53] divided into subgroups following the SAME study IKT approach [57].

### Work Package 1: A Developing Cocreative Process

To reach the overall aim of the SAME study, an intervention to improve medication safety of nursing home residents is aimed in a 2-staged cocreative process (Figure 1). Safety II theory will be used to obtain recommended shift in perspectives in facing health care issues [15,16]. The overall IKT approach of the SAME study will guide the development of cocreators. (Table 1).

#### Stage 1: Qualitative Exploration of Patient Safety Culture in Nursing Homes

The primary objective of stage 1 is to explore patient safety culture in nursing homes, with the perspectives of frontline health care providers being the primary focus. Experienced knowledge will inform the development of the intervention (stage 2) collected through semistructured focus group interviews [58,59]. In addition, field notes will be used as a data source. The medication management process of nursing home residents will be integrated in the development of the semistructured interview guide to ensure the development through medication safety lens of the SAME study.

##### Semistructured Focus Group Interviews

Focus group interviews can be used to gain in-depth understanding of a topic and to identify group norms and cultural values and minimize risk of discrimination regarding reading and writing abilities. Thus, using focus groups to explore patient safety culture could be beneficial with the aim of reaching in-depth knowledge, which is not achieved through quantitative methods [58-60]. All focus group interviews will be facilitated by the external consultant in cocreativity and communication (Table 1). In addition, a researcher (Table 1) will attend to observe and write field notes (Table 1). The first focus group interview will be set to ensure space for the needed adjustments before proceeding with data collection. The municipal risk manager (Table 1) will be invited as an observant of this interview and for a short reflection session at the end of each of the following interviews of approximately 15 minutes.

##### Semistructured Interview Guide

A semistructured interview guide will be developed in collaboration with the research group and an external partner in cocreativity and communication (Table 1). The latter will focus on presentability and general structure of the interview guide, whereas the researchers will account for theoretical information–based and evidence-based outline. To reach in-depth results, 9 intangible domains of organizational culture defined in a recent umbrella review on patient safety culture [44] will inform the interview guide development that will be structured based on Schein’s model of safety culture [45]. Duration of each focus group will be ≤3 hours. This decision was made to face medication safety as a risk area with an expected need for slowly developing a “safe space” for knowledge users not expected to be formerly involved in similar projects, increasing the chance of reaching in-depth results.

##### Study Sample and Size

To help ensure that subgroup norms do not affect data generation negatively and allowing for intimacy, we aim to include a minimum of 3 and ≤5 participants in each focus group. Focus groups will therefore be formed by defined professional subgroups. We aim to include 4 to 6 focus groups, including social and health care assistants, social and health care helpers, general practitioners dedicated to nursing homes, home care nurse and nursing home nurses, and representatives of nursing home residents and their relatives (Table 1). Focus on organizational subgroups could minimize potential negative effects of possible existing hierarchical structures.

##### Outcomes

The primary outcome of stage 1 will be qualitative themes.

##### Data Analysis

Qualitative data will be both field notes and audio recordings that will be transcribed and stored according to current law. Themes will be generated following a triangulated in-person process including researchers with expertise in both qualitative and quantitative methods as well as a representant of end users in the sense of the external consultant in cocreativity and communication, representing cocreators of the SAME study (Table 1). Data analysis will be done following the principles of analyzing in the present [61]. Further validation of the generated themes will be sought through individual triangulation by including researchers representing relevant clinical functions and expertise, including a pharmacist, a nurse, a general practitioner, a qualitative expert, and a quantitative expert.

#### Stage 2: Development of a Knowledge-Based Intervention

In stage 2, the design of the new intervention will be formed. This will be done in a 2-phased process embedded a co-designing process. First, we aim to develop idea generation in a multidisciplinary panel representing a systems view in terms of the medication management process of nursing home residents, and the panel includes nursing home residents and their relatives as well as decision makers. Second, triangulation of ideas will be done with focus on research knowledge. To meet the possibility of using an inadequate number of cocreators to reflect the entire system, the cocreative process will include the investigation of acceptance and usefulness of the intervention through semistructured qualitative focus group interviews with knowledge users and stakeholders in stage 3. The municipal advisory board will play an essential role in stage 2, acting not only as partners in idea generation but also as decision makers in relation to the final intervention design.

##### Data Sources—Collection and Analysis

Data will be qualitative and collected as electronic recordings. Also, a collaborative field note worksheet will be written by facilitators after the workshop. Data analysis will be informed pragmatically by the Delphi method and through a process of data triangulation including stakeholders.

##### Phase 1: Multidisciplinary Panel Workshop

In this phase, we aim to generate ideas based on shared knowledge as an innovative base and to include systems perspective. Experiential knowledge on patient safety culture perceived by nursing home care staff, nursing home residents, and their relatives (Table 1; stage 1, Figure 1) will inform this phase. This will ensure the presence of voices of all knowledge users and minimize potential negative effects of power hierarchical structures. We will ensure acceptable, useful, and meaningful consensus through the presentation of the experiential knowledge from stage 1 as paradoxes by integrating multiple views and possible heterogeneity in the cocreated process. The workshop will be facilitated by the external consultant in cocreativity and communication and 3 representants of the research group (Table 1). The workshop will run over a full working day.

##### Study Sample and Size

A purposive sampling strategy to recruit a multidisciplinary, cross-sectoral panel consisting of knowledge users (Table 1) will be used. This will visualize the relatively invisible team who function in everyday practice and who are implicated in the medication management process of nursing home residents across professions, departments, and health care sectors, including the following:

Social assistants and health assistants (n=2)Social helpers and health helpers (n=2)Municipal management (n=2)Nursing home management (n=2)Nursing home general practitioners (n=2)Home care nurses and nursing home nurses (n=2)Risk managers employed at hospital and by the municipality (n=2)Relatives of nursing home residents (n=2)Representants of nursing home residents (“DaneAge association” and “Senior-council, Denmark”; n=2)

##### Outcome, Data Sources, and Collection

The primary outcome of phase 1 will be generation of ideas to improve medication safety, focusing on shared knowledge. A part of a cocreative process, data collection methods have not been predefined but will be developed as part of the research process. The external consultant in cocreativity and communication (Table 1) will play a key role. Both electronic records and field notes will be used as data sources. Results will inform phase 2.

##### Phase 2: The Co-designing Process—Data Sources, Collection, and Analysis

Data will be qualitative and collected as electronic recordings. In addition, a collaborative field note worksheet will be written by facilitators during and after the workshop. Data analysis will be done in a process of data triangulation including relevant stakeholders.

First, a preliminary intervention will be co-designed based on ideas generated at the workshop. Qualitative data will be analyzed guided by “analyzing in the present” [61] based on a triangulated process between participating facilitators after the workshop, following the cocreative approach including the external consultant in cocreativity and communication (Table 1).

Second, a co-designing phase including researchers and decision makers (Table 1) will be done to undertake an organizational and contextualized perspective. This will increase feasibility and acceptability potential of the final intervention design to be evaluated in the RCT (stage 3). Purposely sampled cocreators will be consulted in person through the presentation of the preliminary intervention, thereby leaving room for revision and correction. We aim to include cocreators having expertise in general practice, nursing, and pharmacology, in addition to those from qualitative and quantitative research fields in this phase.

Third, the municipal advisory board will be consulted, as their knowledge concerning organizational factors implicating the intervention will be essential to ensure a local contextualized, final intervention design.

Finally, the intervention will be designed by the research team in terms of explicating the decisions made by all the cocreators. The final intervention will be presented to the municipal advisory board, minimizing the risk of misinterpreted information and increasing the potential for adaptability through management support.

### Work Package 2: Evaluation of Intervention and Understanding of Patient Safety Culture

#### Stage 3: Quantitative Evaluation of the New Intervention in an RCT

In stage 3, we will evaluate the new intervention in a randomized controlled study set at nursing homes. Data on primary outcome will be collected at baseline before rollout of the intervention and at 6-month to 9-month follow-up according to intervention rollout at individual participating nursing homes. Data on secondary outcomes will be collected during the intervention period.

##### Study Sample and Size

A total of 36 public nursing homes were registered within the Municipality of Aalborg in 2021. We expect to recruit a minimum of 22 nursing homes to participate in this phase. Inclusion criteria are the following: to be eligible for inclusion within this study, nursing homes must be supported by a general practitioner registered by the Municipality of Aalborg. Exclusion criteria are the following: if a conflict appears, for example, in relation to other initiatives targeting medication, the Municipality will ensure exclusion of specific nursing homes. Nursing home care staff will be included according to the overall eligibility criteria and definitions defined in Table 1.

As no other studies have investigated the effect of a complex intervention in a mixed methods study design in primary care on SAQ, the sample size cannot be based exclusively on previous study outcomes. We aim to recruit as many respondents as possible from the included nursing homes.

Based on previous studies focusing on related health care setting and culture, we expect mean scale scores of SAQ of 32 to 75 [62,63], and we expect to find an increase of at least 4.0. We expect a lower SD than that reported in previous studies, as these studies have investigated more variable groups of professions. The overall SD (all domains) in home care services have been reported as 9.8 [62]. Thus, with a power of 0.8, significance level (α) of .05, and an expected SD of 9.8, it has been estimated that 192 respondents (96 respondents in the intervention group and 96 respondents in the control group) will be sufficient.

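### The claim that 192 respondents suffice for 80% power holds only if staff of the same nursing home respond independently, and the plan recruits and delivers by home

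*Protocol article*

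**What the plan says.** All sample size inputs are in the stage 3 section on study sample and size of the protocol article: "with a power of 0.8", a "significance level (α) of .05", "an expected SD of 9.8", and a target stated as "we expect to find an increase of at least 4.0". The conclusion is: "it has been estimated that 192 respondents (96 respondents in the intervention group and 96 respondents in the control group) will be sufficient". The calculation mentions no ICC, design effect, number of homes or respondents per home.

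The same section counts participation in homes: "We expect to recruit a minimum of 22 nursing homes to participate in this phase", out of 36 public homes in the municipality. Inclusion and exclusion criteria are also set for homes. The opening paragraph of stage 3 describes a randomised study located at nursing homes and times follow-up "according to intervention rollout at individual participating nursing homes". No sentence says outright whether homes or staff are randomised.

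The primary outcome is the SAQ-DK mean scale score, reported individually by care staff and managers. The Statistical Analysis section names Poisson regression for comparing the groups and does not mention home. The sample size section also sets the aim of recruiting as many respondents as possible, without giving a number.

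**The concern.** The calculation counts people, while the trial is run through homes. Staff of one home share managers, the timing of the rollout and the culture that the questionnaire measures. The Patient Safety Culture section of the Introduction itself defines the construct as values held in common by members of an organisation. Positive correlation within homes is therefore to be expected, and each further respondent from a home adds less information than an independent one.

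This is the only power statement for the primary outcome. If it is too favourable, a null result could be read as coming from an 80%-powered comparison when the power was lower. If the analysis also ignored home, a positive result would carry too small a p-value and too narrow a confidence interval.

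**Working it through.** **Inputs from the article.** Power 0.80; α = 0.05 (sidedness not stated); difference 4.0; SD 9.8; 96 per group, 192 in total; 22 homes at minimum, 36 at most.

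**Assumed.** ICC of 0.02, 0.05 or 0.10, because the article gives none; equal numbers of respondents per home; homes allocated 1:1.

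**1. Reproducing 192.** Normal formula: n per group = 2 × (1.960 + 0.842)² × 9.8² / 4.0² = 94.2, so 95. With the t distribution, power is 79.9% at 95 per group and 80.3% at 96, so 96 is the first size to reach 80%. A one-sided test would need only 75. The stated figure is thus the two-sided independent-respondent result, with a design effect of 1.

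**2. Slack.** By the normal formula, 2 × 94.2 = 188.4 independent respondents are needed, and 192 / 188.4 = 1.019. At 22 homes the mean is m = 192 / 22 = 8.73 per home, so the slack is used up at an ICC of 0.019 / 7.73 ≈ 0.0024.

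**3. Power at 192 with clustering.**
- Design effect: DE = 1 + (m − 1) × ICC.
- Standard error of the difference: SE = 9.8 × √(4 × DE / 192).
- Normal power: Φ(4.0 / SE − 1.960).
- t-based power: noncentral t with noncentrality 4.0 / SE and degrees of freedom = homes − 2.

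Worked case, 22 homes and ICC 0.05: DE = 1 + 7.73 × 0.05 = 1.386; SE = 9.8 × √(4 × 1.386 / 192) = 1.666; 4.0 / 1.666 = 2.40; normal power = Φ(0.44) = 67%; with 20 df, 63%.

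| Homes | m | ICC | DE | Effective N (192 / DE) | Power, normal | Power, t (homes − 2 df) |
|---|---|---|---|---|---|---|
| 22 | 8.73 | 0.02 | 1.15 | 166 | 75% | 71% |
| 22 | 8.73 | 0.05 | 1.39 | 138 | 67% | 63% |
| 22 | 8.73 | 0.10 | 1.77 | 108 | 57% | 52% |
| 36 | 5.33 | 0.02 | 1.09 | 177 | 77% | 75% |
| 36 | 5.33 | 0.05 | 1.22 | 158 | 73% | 70% |
| 36 | 5.33 | 0.10 | 1.43 | 134 | 66% | 63% |

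The normal column isolates the effect of correlation. The t column adds the cost of having few homes: with 20 df, power is 76.7% even at ICC 0.

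**4. More respondents per home.** At an assumed 20 per home in 22 homes (440 in total), DE = 1.38 / 1.95 / 2.90 and power with 20 df is 93% / 83% / 67% at ICC 0.02 / 0.05 / 0.10.

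**5. Type I error if home were ignored.** The actual level of a nominal 5% test is 2 × [1 − Φ(1.960 / √DE)]. For 192 respondents in 22 homes it is 6.8% / 9.6% / 14.1%; in 36 homes, 6.0% / 7.6% / 10.2%. At 20 per home in 22 homes it is 9.5% / 16.0% / 25.0%. Larger samples per home help power but worsen an unclustered test.

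**The case against.** The strongest reply is that 192 is a floor. The article wants as many respondents as possible, and 22 homes is a minimum. Step 4 shows that more staff per home can bring power back above 80% at ICC 0.02 and 0.05. This stands, and it limits the point to the sentence that calls 192 sufficient. A reader might infer that the trial is underpowered; the documents do not show that, because they give no ICC and no expected number of respondents. Nor do they show that 80% power is out of reach at ICC 0.10. With 20 df, holding homes at 22 would require about 3,500 respondents, but with all 36 homes (34 df) about 404 would do.

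A second reply is that the full analysis plan is not shown and may account for home. That also stands. A reader might infer from the Poisson sentence that the type I error will be inflated, but a condensed article can leave a home effect to the analysis plan. The inflation figures are therefore conditional. This reply does not rescue the sample size, since an analysis that properly accounts for home is what gives the power shown in step 3.

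Third, randomisation by home is an inference. It is a strong one, given recruitment and rollout by home, but the authors must state the unit. Even with individual allocation, delivery by home would leave independence to be justified.

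Finally, the article expects a lower SD than earlier studies found, and baseline scores are collected. Either could recover some power. Neither enters the stated calculation, which uses 9.8 and no baseline adjustment.

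**Conclusion.** The point holds in a limited form. The arithmetic behind 192 is correct, but it rests on independent respondents, which does not fit a trial that recruits and delivers by home and measures a shared culture. With that number, 80% power fails for all but a negligible ICC. Over an assumed ICC of 0.02 to 0.10, power at 192 runs from 75% down to 57% in 22 homes and from 77% down to 66% in 36 homes by normal approximation, and lower with small-sample degrees of freedom. The direction follows from the article's own inputs; the size depends on the assumed ICC, equal home sizes and allocation by home. Type I error inflation is a secondary consequence, arising only if home is left out of the analysis.

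**What to change.** - State the unit of randomisation.
- Replace the sufficiency sentence with the power that the actual number of homes and the expected follow-up respondents give, over a stated ICC range such as 0.02 to 0.10.
- Account for home in the primary analysis, through a random intercept or home-level summaries, with small-sample degrees of freedom (about homes minus 2).
- Report the observed ICC.

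The cost is some wording and one model term. Baseline data were collected in January 2022, but the changes can be made before the final analysis. The quoted power becomes less favourable and confidence intervals widen. Restating the power needs no extra recruitment; keeping 80% power would take more than 192 respondents.

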##### Outcomes

The initial problem statement that emerged from the Municipality of Aalborg was that adverse events were increasingly reported, yielding a legally bound challenge that is not yet overcome. Thus, the Municipality sought help for lowering the number of medication errors and unsafe medication practices through collaboration. Although reporting adverse events is an intended goal in safety terms in Denmark, the number of adverse events is not a proper estimate of medication safety.

As a proxy for the overall medication safety, including medication errors, the SAQ has been suggested. A Danish reliable and valid version is available (Danish Safety Attitudes Questionnaire, SAQ-DK). An increase in SAQ-DK would indicate a decrease in medication errors, whereas a decrease would indicate a worsening. We are aware of using the SAQ-DK as the primary outcome with precaution, as the intended increase in reporting adverse events within primary care is still an ongoing issue. However, to the best of our knowledge, no other more suitable measure is available, and therefore, we chose the SAQ as the most reliable and relevant proxy for medication safety in the SAME study.

The primary outcome will be focused on the nursing home frontline, including nursing home care staff’s and nursing home managers’ (Table 1) self-reported perceptions of patient safety culture measured as mean scale SAQ-DK score [36]. The SAQ-DK will be adapted for use in Danish primary health care settings, including nursing homes following the cocreative approach of the SAME study.

Secondary outcomes will include the following: qualitative—perceptions of patient safety culture of relevant cocreators collected through semistructured focus group interviews or individual interviews, depending on the results of the research process; quantitative—register data; that is, sociodemographic data and data on health-related outcomes will be collected at baseline and at follow-up. Data will be collected from relevant Danish registries.

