Thus, medication errors and unsafe medication practices continue to concern health care systems worldwide, including nursing home settings. However, earlier research clearly reflects a gap in the knowledge about interventions to improve medication safety in nursing home settings. Patient safety culture is acknowledged as a key to patient safety, both in terms of improvement and effect evaluation [16,27-29] and has been associated with medication errors, also showing improvement potential [19,30]. In 2021, a guiding report on avoiding harm in health care added the importance of focus on primary health care settings, involvement of stakeholders, and cocreation to conquer the challenge of patient safety, including medication safety [16]. Moreover, safety cultures were recommended to be integrated within research designs and as for efforts within health care organizations [16]. This is in alignment with the most recent health work paper by the Organization for Economic Cooperation and Development stating patient safety culture as a recognized factor of importance at all levels of health care. Moroever, instruments to measure patient safety cultures are already in use in 20 of 24 member countries [20].

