#### Patient Safety Culture

Patient safety culture is a complex phenomenon that is thought as a subclass of organizational cultures referring to the safety culture related to patients [21]. It is defined as “the values shared among organization members about what is important, their beliefs about how things operate in the organization, and the interaction of these with work unit and organizational structures and systems, which together produce behavioral norms in the organization that promote safety” [31]. Instruments that aim to capture reflections of patient safety cultures have been developed and validated [20,32], with one of the most widely translated and adapted being the “Safety Attitudes Questionnaire” (SAQ), originally developed in the United States in 2006 [33]. The SAQ can be used with dualistic perspectives both to compare different health care employees perceptions and to monitor changes over time [32]. In addition, it allows for comparison between large numbers of sites across settings [33]. Although evidence is sparse and contradictory [34], there is evidence indicating that SAQ is a proper proxy measure of patient safety [35]. SAQ scores have been reported to be directly associated with patient outcomes [32]. The SAQ has been adapted and validated for use in both secondary care and primary care settings [36-40], including Western European nursing homes [38,41] and Danish hospital settings [36].

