### Prior Work

International studies have found lower measures of patient safety culture in nursing homes compared with hospital settings [42,43]. Importantly, no single instrument can capture the complexity of safety culture [44], which is regarded a multilayered construct. Outermost layers are considered to be visible and measurable (layers 1 and 2), whereas the deepest layer holding the essence of a culture is measurable only through qualitative means (layer 3) [45]. Layer 3 has not been reflected by earlier research [46], resulting in evidence on patient safety culture in nursing homes being mainly based on quantitative studies. This gap in knowledge could weaken medication safety improvement initiatives [45] and implies a need for in-depth exploration of patient safety culture, including qualitative methods [44-46]. An integrative mixed methods approach to analysis could further strengthen results to gain comprehensive understanding of patient safety culture as a target of intervention to improve medication safety [47].

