#### Stage 4: Mixed Methods Integrative Analysis of Patient Safety Culture: Mixed Methods Analysis

Through a mixed methods integrative analysis, the SAME study aims to gain comprehensive understanding of patient safety culture as a multilayered construct and target of medication safety intervention (stage 4) via different data sets, including (1) a quantitative questionnaire on nursing home care staff and nursing home management’s (Table 1) self-reported perceptions of patient safety climate (SAQ-DK), (2) qualitative data on patient safety culture, and (3) qualitative data from individual interviews with knowledge users. The different sets of data will be collected and analyzed separately for final integration through use of “joint display of data” [67] in a mixed methods analysis. Results could lead to the development of a new theory on patient safety cultures in Danish nursing homes, informing future research and clinical practice in the area.

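### The plan reads a rise in SAQ-DK as fewer medication errors, but it calls the proxy evidence sparse and contradictory and lists no outcome that counts errors

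*Protocol article*

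**What the plan says.** The Outcomes section under Stage 3 names the SAQ-DK mean scale score, completed by nursing home care staff and managers, as the primary outcome. It presents the questionnaire as a proxy for overall medication safety and then gives a rule that runs in both directions: "An increase in SAQ-DK would indicate a decrease in medication errors, whereas a decrease would indicate a worsening". The same paragraph adds a caution, "We are aware of using the SAQ-DK as the primary outcome with precaution", and says that the authors know of no more suitable measure.

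The Introduction describes the evidence behind the proxy. Under Patient Safety Culture it says: "Although evidence is sparse and contradictory [34], there is evidence indicating that SAQ is a proper proxy measure of patient safety". The next sentence is favourable: "SAQ scores have been reported to be directly associated with patient outcomes [32". Earlier in the Introduction, patient safety culture itself "has been associated with medication errors, also showing improvement potential [19,30".

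On data about residents, Outcomes sets aside the number of reported adverse events as an unsuitable estimate of medication safety. Safety Assessments and Effects lists four kinds of register data: medication (number and type), health care contacts, diagnoses and mortality. Groups are to be compared on these with descriptive statistics.

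**The concern.** The rule turns a difference in a staff questionnaire score into a statement about medication errors among residents. It carries no qualification, although the Introduction treats the proxy evidence as contested.

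The Municipality came to the researchers because it wanted fewer medication errors and unsafe practices, and the study is built to inform decision makers. If the rule is followed, a higher score in the intervention arm is read as fewer errors and a lower score as a worsening. Scores could move in either direction without any change in errors, and the trial has no error measure that would show it.

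**Working it through.** The point is one of interpretation. The only figure to reproduce is the sample size, which shows what the trial is planned to detect.

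**1. The plan's own figure.** Inputs from Study Sample and Size (Stage 3): difference 4.0, SD 9.8, power 0.8, α 0.05. The article does not state sidedness; two-sided reproduces its figure.

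- Normal approximation: n per group = 2 × (1.960 + 0.842)² × 9.8² / 4.0² = 2 × 7.85 × 96.04 / 16 ≈ 94.2, rounded up to 95, or 190 in total.
- Two-sample t-test: 95.2, rounded up to 96, or 192 in total, as stated.
- Power with 96 per group (normal approximation): 0.807.

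The 192 is therefore a calculation for 4.0 points of SAQ score, a standardised difference of 4.0 / 9.8 = 0.41. Medication errors do not enter it.

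**2. Converting points to errors.** This would need a slope or correlation between change in score and change in error rate. The article gives none, so 4.0 points cannot be expressed as a reduction in errors.

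**3. What each passage supports, set against the rule.**

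- *Patient Safety Culture:* some evidence for the questionnaire as a proxy of patient safety in general, with the body of evidence conceded to be sparse and contradictory. It does not speak of medication errors specifically.
- *Patient Safety Culture, next sentence:* a reported association of scores with patient outcomes.
- *Interventions to Improve Medication Safety in Nursing Homes:* a reported association of safety culture with medication errors. A reported association does not show that a change in score produced by an intervention means a change in errors.
- *Patient Safety Culture and Outcomes:* the Danish version was validated in hospital settings and is still to be adapted for nursing homes. The rule is thus applied to an instrument one step removed from that validation.
- *Stage 4:* the same instrument is described as measuring "self-reported perceptions of patient safety climate (SAQ-DK"), which is a statement about perception.

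**4. Whether the trial could check the rule.** Reported adverse events are set aside. Of the four register categories, none is a count of medication errors. Number and type of medication is the closest, but it describes what residents receive, and the article gives no favourable direction for it. The inference therefore cannot be tested inside the trial.

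**The case against.** The strongest defence is that the sentence belongs to a paragraph that openly calls the questionnaire a proxy, says it is used with caution and reports that nothing better is known. The wording gives the direction in which the proxy points and does not claim certainty. The Introduction also cites supporting evidence. Finally, the primary outcome is defined as staff perceptions, and results are to be presented as score means and SDs, so no claim about errors has yet been made.

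Much of this stands, and it rules out several stronger readings that a reader might infer:

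- *That the trial measures no resident outcome.* It does, through the registers. What is unmeasured is medication errors.
- *That the article offers no support for the link.* It reports associations with both patient outcomes and medication errors.
- *That a positive trial will claim fewer errors.* That is a forecast. The abstract and conclusions contain no such statement.
- *That the shift would be unblinded opinion.* The article says nothing on blinding.
- *That the risk of a wrong reading can be quantified.* If changes in score and errors in one home were bivariate normal, centred on no change, with assumed correlation strength 0.1, 0.3 or 0.5, a rise in score would go with fewer errors with probability 0.5 + arcsin(r)/π = 0.53, 0.60 or 0.67. Every input is assumed, and the figure describes one home, whereas the trial compares arms across at least 22 expected homes. It carries no weight here.

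The defence does not rescue the sentence itself. The caution is explained by the continuing push for more adverse-event reporting, not by weakness of the proxy evidence. The lack of a better measure can justify choosing SAQ-DK, but not reading it as a statement about errors.

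**Conclusion.** The concern holds in a limited form. The Outcomes section states an unqualified two-way reading of SAQ-DK in terms of medication errors. The article's evidence is mixed, the score is self-reported by staff and managers, and no listed outcome counts errors. A conclusion about errors drawn under this rule would not be supported by the data collected.

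The choice of SAQ-DK as primary outcome is not at fault, and neither the sample size arithmetic nor the collection of register data is challenged on this point. The size of the overreach cannot be given, because no figure links score to errors. The verdict rests only on the article's text, with the register list taken as the complete set of quantitative resident outcomes. It is worth correcting before results are reported, because the correction limits what the trial may conclude.

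**What to change.** Keep SAQ-DK as the primary outcome. In the Stage 3 Outcomes section, replace the interpretive sentence with:

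*A between-arm difference in SAQ-DK will be interpreted as a difference in staff-perceived patient safety culture; it will not by itself be taken as evidence of fewer or more medication errors.*

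Report the register outcomes from Safety Assessments and Effects beside the primary result, descriptively as planned. Do not make a claim about errors depend on one of them pointing the same way. None is an error measure, no favourable direction is stated for medication number and type, and with no test or margin agreement could arise by chance about half the time.

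The cost is one sentence. It needs no new data and no change to the sample size or primary outcome. The downside is a more modest headline claim.
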